#### Sensitivity analysis B

To put the discrepancies between the AI system and the reference standards in the context of interobserver variation between pathologists, we will quantify all-against-all pairwise agreements in panels consisting of pathologists and the AI system.

For the primary objective, the analysis will be conducted on subsets of the STHLM3 (ImageBase) and RUMC (PANDA Radboud) internal validation cohorts and on the full UKK and WNS external validation cohorts, which were assessed by a panel of pathologists and have per-pathologist grades available in addition to their consensus (see table 2). For the secondary objectives of cribriform cancer and PNI detection, the analysis will be conducted on subsets of the STHLM3 internal validation cohort, assessed by panels of pathologists (see table 3).

We will calculate the average pairwise agreement (QWK and LWK for the primary objective, unweighted Cohen’s kappa for the secondary objectives) for all the pathologists in the panels, including the AI system, and compare the average AI-pathologist agreement to the average pathologist-pathologist agreement. CIs will be computed using bootstrapping, as detailed in a previous study.^47^

#### Sensitivity analysis C

To assess the sensitivity of the results to different pathologists providing the cohort-specific reference standards and to isolate differences in observed AI performance due to varying reference standards from those due to imperfect generalisation to different labs and scanners, we will repeat the primary analysis using a consistent reference standard. We will measure the agreement between the AI system and the uniform reference standard set by the lead pathologist (LE) on subsets of the SUH and RUMC internal validation cohorts and the AUH, MLP, MUL, SCH, SFI, SFR and SPROB20 external validation cohorts. While the original reference standards were varyingly reported either on the level of slides, anatomical locations, or patients, LE’s reassessments are consistently reported on slide level. See table 2 for a summary of the reassessed subsets and reference standard protocol in online supplemental appendix 2 for details on the case selection for each cohort.

Furthermore, we will measure the agreement in ISUP grades (QWK and LWK) between the original reference standards and the lead pathologist on the reassessed subsets of each cohort. To facilitate this comparison for cohorts with original reference standards provided on anatomical location or patient level (whereas the grading by LE is on slide level), the location or patient level grading by LE will be obtained as the maximum ISUP grade over all slides belonging to a location or patient.

#### Sensitivity analysis D

We will perform a sensitivity analysis that involves a reassessment of slides where the AI system committed clinically significant errors by repeating the primary analysis against the updated reference standard. This analysis aims to evaluate what portion of clinically significant errors can be attributed to data quality issues, such as mistyped information in the reference standard tables, mixed-up slide identifiers or WSI scanning issues in cases where the original reference standard was set using a microscope. Significant errors are defined as cases where the AI model predicts a slide as benign, but the reference standard indicates ISUP grade ≥2, or conversely the AI predicts a slide as ISUP grade ≥2, but the reference standard indicates benign. These slides will be reassessed by the lead pathologist (LE) and/or other experienced uropathologists, blinded to the original reference standard and the AI output. If a slide cannot be assessed due to, for example, poor focus, it will be excluded. The evaluation will be conducted on the internal and external validation cohorts, on both the full cohorts after updating the reference standards, and on only the updated subsets. Additionally, during this analysis, pathologists will report whether any of the cases with clinically significant errors represent ductal adenocarcinoma (DAC). Despite being the second most common subtype of prostate cancer after acinar adenocarcinoma, DAC only accounts for 0.17% of prostate cancers^48^ and may, therefore, be challenging for AI to detect due to the limited amount of training data.

#### Sensitivity analysis E

We will perform a sensitivity analysis that involves the exclusion of samples reported by the pathologists as ‘borderline’ for cribriform cancer or PNI, followed by repeating the secondary analyses concerning these objectives. Conducting the analysis only on samples indicated as negative or positive will provide an estimate of the AI system’s performance in detecting cribriform cancer and PNI less affected by the uncertainty and subjectivity in the definition of these entities. We will additionally quantify the prevalence of borderline diagnoses among slides initially classified as false positives versus true negatives to quantify whether borderline cases are overrepresented among false positives. This would indicate that false positives mainly arise due to uncertainty of the reference standard.

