### Secondary analysis: cribriform cancer detection

We will quantify the concordance of the AI system’s prediction of the presence of cribriform cancer with the reference standards in those internal and external validation cohorts where a reference standard is available (AMU, MUL, SCH, STHLM3, SUH). The tuning set has an insufficient number of cribriform samples for evaluation and will be included in the training. The concordance will be quantified using unweighted Cohen’s kappa. In addition, we will also report AUROC, sensitivity (true positive rate), specificity (true negative rate) and confusion matrices. Slides reported as borderline for cribriform cancer will be considered negative. The analysis will be conducted on slide level. CIs will be computed using the non-parametric bootstrap over cases.

The model will be developed and validated to identify cribriform growth pattern, irrespective of whether it occurs within acinar adenocarcinoma (ie, invasive cribriform) or intraductal carcinoma (IDC) (ie, non-invasive cribriform). The rationale for this is that these entities are often assessed and reported together for further prognostication and treatment planning. This practice is supported by the 2019 ISUP consensus, which recommended incorporating IDC into the Gleason grading when present alongside invasive carcinoma.^46^

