### Secondary analysis: PNI detection

We will quantify the concordance of the AI system’s prediction of the presence of PNI with the reference standards in those internal and external validation cohorts where a reference standard is available (MUL, SCH, STHLM3 and SUH). The tuning set has an insufficient number of PNI samples for evaluation and will be included in the training. The concordance will be quantified using unweighted Cohen’s kappa. In addition, we will also report AUROC, sensitivity (true positive rate), specificity (true negative rate) and confusion matrices. Slides reported as borderline for PNI will be considered negative. The analysis will be conducted on slide level. CIs will be computed using the non-parametric bootstrap over cases.

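### Sensitivity analysis E reads over-representation of borderline slides among false positives as showing that false positives mainly come from reference uncertainty, which does not follow

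*Protocol article*

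**What the plan says.** The two secondary detection analyses settle how borderline slides are coded. In the cribriform section: "Slides reported as borderline for cribriform cancer will be considered negative". In the PNI section: "Slides reported as borderline for PNI will be considered negative". An AI-positive borderline slide is therefore a false positive in the main secondary analyses.

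Sensitivity analysis E does two things. It repeats both analyses after removing borderline slides. It will also "quantify the prevalence of borderline diagnoses among slides initially classified as false positives versus true negatives", the stated purpose being "to quantify whether borderline cases are overrepresented among false positives". The next sentence gives the reading to be placed on that finding: "This would indicate that false positives mainly arise due to uncertainty of the reference standard". No condition is set on how large a part of the false positives must be borderline.

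**The concern.** The condition is relative: borderline slides are commoner among false positives than among true negatives. The conclusion is about a majority: most false positives have a particular origin. The first does not imply the second.

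There is also a step from association to cause. Borderline slides resemble positives, so a model that responds to the target morphology will tend to flag them more often than clear negatives, even if its specificity on clear negatives is poor. The condition is therefore likely to be met by good and mediocre models alike. A borderline false positive may reflect a low AI threshold as well as an uncertain reference.

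The Study status section says the final evaluation will follow the prespecified plan. Taken literally, the sentence would let a report on two of the three secondary objectives attribute most false positives to the reference standard when most could be AI errors on slides that the pathologists called plainly negative.

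**Working it through.** The protocol states no figure here, so there is nothing to reproduce. The check asks what the stated condition requires and what the stated conclusion requires.

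**Inputs.** From the protocol: borderline slides count as negative, and the comparison is between false positives (FP) and true negatives (TN). Not in the protocol, hence assumed: the borderline share of reference-negative slides, *b* (5% to 30%); the AI-positive rate in borderline slides, *fb* (20% to 50%); and in clear negatives, *fc* (5% to 10%).

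**Formulas.**

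- Borderline share of FP = b·fb / [b·fb + (1−b)·fc]
- Borderline share of TN = b·(1−fb) / [b·(1−fb) + (1−b)·(1−fc)]
- Over-representation (first share above second) holds exactly when fb/(1−fb) > fc/(1−fc), that is, when fb > fc.
- A borderline majority of FP needs b·fb > (1−b)·fc, that is, fb/fc > (1−b)/b.

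The condition thus needs a ratio fb/fc above 1. The majority needs:

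| b | (1−b)/b |
|---|---|
| 5% | 0.95/0.05 = 19 |
| 10% | 0.90/0.10 = 9 |
| 20% | 0.80/0.20 = 4 |
| 30% | 0.70/0.30 = 2.33 |

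**Worked case (assumed).** 200 reference-negative slides, b = 10%, fb = 30%, fc = 10%.

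- Borderline: 20 slides, of which 20 × 0.30 = 6 FP and 14 TN.
- Clear negative: 180 slides, of which 180 × 0.10 = 18 FP and 162 TN.
- Borderline share of FP: 6/24 = 25%. Of TN: 14/176 = 8.0%.
- Odds ratio: (6/14)/(18/162) = 3.86.
- Specificity with borderline coded negative: 176/200 = 88%. With borderline excluded: 162/180 = 90%.

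Borderline slides are clearly over-represented, yet 18 of 24 false positives (75%) are clear negatives, and removing borderline slides lowers the false-positive rate only from 12% to 10%.

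**Range.** Borderline share of FP, in percent, by assumed fb/fc (both in percent):

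| b | 20/10 | 30/10 | 30/5 | 50/10 | 50/5 |
|---|---|---|---|---|---|
| 5% | 9.5 | 13.6 | 24.0 | 20.8 | 34.5 |
| 10% | 18.2 | 25.0 | 40.0 | 35.7 | 52.6 |
| 20% | 33.3 | 42.9 | 60.0 | 55.6 | 71.4 |
| 30% | 46.2 | 56.3 | 72.0 | 68.2 | 81.1 |
| Odds ratio | 2.25 | 3.86 | 8.14 | 9.0 | 19 |

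Borderline slides are over-represented in all 20 scenarios. They are under half of the false positives in 12 and over half in 8.

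**The case against.** The best defence is that the analysis already produces the figures that would correct the sentence. The borderline prevalence among false positives is itself the share that 'mainly' calls for, and it is to be reported for each group. The repeat without borderline slides gives specificity and confusion matrices on clear negatives, with bootstrap intervals as in the main secondary analyses. The wording is also mild: it says what a finding would indicate, with no test, cut-off or decision attached. AI-positive calls that concentrate on slides the pathologists could not settle are relevant evidence of uncertainty in the reference. All of this stands, and it keeps the point small. It does not rescue the inference, because the sentence attaches the majority conclusion to the relative comparison and not to the share.

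A reader might infer more than the documents support:

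- *That the plan moves AI errors out of the results.* It does not. The main analyses count every AI-positive borderline slide against the AI, and Sensitivity analysis E does not replace them.
- *That the needed figures are missing.* They are planned; only an interval on the share is not mentioned.
- *That most false positives will in fact be clear negatives.* The protocol gives no borderline counts or AI-positive rates, and in 8 of the 20 assumed scenarios borderline slides are the majority.
- *That 'mainly' must wait until a lower confidence limit exceeds 50%.* That is one possible criterion, and nothing in the protocol requires it.

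**Conclusion.** The point holds as an error of interpretation. Over-representation relative to true negatives does not show that false positives mainly arise from reference uncertainty. The logical gap does not depend on any assumed rate: one statement needs fb > fc, the other needs fb/fc > (1−b)/b, and these differ whenever borderline slides are fewer than half of the reference negatives. How far the sentence could mislead does depend on rates that the protocol does not give. Even a borderline majority would show where the false positives fall, and would not by itself prove why. The severity is minor: no primary result, main secondary estimate or planned calculation is affected.

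**What to change.** Change the one sentence in Sensitivity analysis E to say that over-representation would be consistent with reference uncertainty contributing to false positives. Base any statement that false positives mainly arise this way on the absolute share of false positives that are borderline, which is already to be quantified, and add a confidence interval to it. Read that share beside the specificity on clear-negative slides from the already planned repeat without borderline slides.

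This needs no new data and no new analysis beyond the interval. The cost is a less favourable reading of the false positives than the present sentence allows.

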### Exploratory analysis: evaluate visualisations of the AI output

We will output visualisations of the AI system’s predictions to highlight areas on each slide containing different Gleason patterns, cribriform cancer or PNI. The visualisations will be assessed qualitatively by the lead pathologist (LE) and/or other experienced uropathologists for concordance with their assessments. We may additionally quantify the rate of agreement between the AI system and the pathologists by collecting region annotations to serve as a reference standard, and by calculating the pixel-wise sensitivity, specificity, intersection over union or other suitable metrics.

### Exploratory analysis: evaluate the impact of tissue segmentation algorithms

Detecting tissue from the background to only apply the rest of the analysis on tissue pixels is a common preprocessing step for most computational pathology algorithms. While this task of tissue segmentation may seem trivial, many modern AI algorithms reach such low error rates in their main task that any errors in tissue detection can contribute to the overall model performance in a considerable way. In particular, missed tissue poses a risk of false negative diagnoses, if this leads to the exclusion of malignant tissue from the analysis. We will evaluate the effect of tissue segmentation on the overall performance of the AI system in terms of the primary and secondary objectives by comparing two different tissue segmentation algorithms. One of the algorithms represents classical image processing and relies on filtering and thresholding the image.^15^ The other algorithm is a trained deep learning-based segmentation model. We will apply both algorithms to perform the tissue segmentation during model training and validation and compare the results on the internal and external validation cohorts.

### Exploratory analysis: evaluate end-to-end versus transfer-learning-based models

Recently, so-called foundation models trained in a self-supervised manner on large and heterogeneous datasets have been proposed as generally applicable solutions to diverse tasks in computational pathology as an alternative to tissue type or task-specific models.^49^ We aim to compare our end-to-end trained prostate cancer-specific model to transfer-learning-based models relying on state-of-the-art foundation models for histopathology. We will apply a suitable foundation model as a feature extractor and train an additional classifier to adapt the model to the task of diagnosis and Gleason scoring of prostate biopsies. For this transfer learning step, we will use the same development cohorts as for the end-to-end trained model. We will then evaluate the model on the same internal and external validation cohorts as the end-to-end trained model for a direct comparison.

### Exploratory analysis: evaluate the impact of physical colour calibration

Variations in the reproduction of colour across different digital pathology scanners may pose a problem for AI, leading to inconsistent model outputs depending on the scanner used for slide digitisation. A physical calibrant in the form of a spectrophotometrically characterised slide has been proposed as a means for standardising the colour characteristics of WSIs acquired with different scanners.^50^ We will evaluate the impact of applying physical colour calibration on the performance of the AI model on those internal and external validation cohorts where the calibrant slide could be scanned on the same scanner as the prostate biopsies to allow calibration.

### Confounding factors

Statistical confounding, or spurious correlations, in the training and validation data of predictive models, may lead to ‘shortcut learning’ or so-called ‘Clever Hans predictors’,^51^ where overly optimistic performance on validation data is seen as the result of the model taking advantage of unintended correlations between some attributes of the data and the correct labels. Such biases are also common in digital pathology datasets.^20 22^ We have carefully considered the potential presence of such biases in our cohorts and taken the steps described below to mitigate the issue.

An important confounding factor is the scanner instruments used for digitising various subsets of our data cohorts. Patients in different cohorts and subsets of cohorts have been sampled in varying ways, leading to differences in the compositions of these groups in terms of GS and ISUP grade distribution. These correlations between specific clinical sites or scanner instruments and the target labels can create biases during training since the model could learn to associate the appearance of WSIs obtained from a specific site or with a specific scanner with a higher or lower likelihood of a particular diagnostic or grading outcome. If the same bias is present in validation data, this will lead to overly optimistic results. Conversely, if the bias present in training data is not present in the validation data, a model relying on these spurious correlations will perform poorly. The main approach we have taken to mitigate the risk of overly optimistic validation results is relying on fully external validation data. The external validation cohorts represent patients, clinical sites, laboratories and scanners not present in the training data. This minimises the risk of the same spurious correlations appearing in both training and external validation data. When it comes to discouraging the model from learning any spurious correlations between laboratories or scanners and the target labels, which could result in suboptimal performance in the absence of these correlations, we will apply a sampling scheme which removes the correlations between these variables during model training.

Another common confounding factor we have identified is markings on the slides. Pathologists often place pen marks on the glass slides to indicate cancerous regions. These can lead the AI model to directly associate the presence of markings with the presence of cancer, or indirectly to associate image quality artefacts such as poor focus caused by the pen marks with a higher likelihood of cancer being present. We have mitigated these issues by (1) applying tissue detection and masking of background pixels as an image preprocessing step, ensuring that pen markings adjacent to tissue will not be shown to the model, (2) washing and rescanning of slides where pen markings are placed on top of tissue or caused focusing issues or (3) excluding slides where neither of the first two options was possible. The first approach of background masking is applied to all the WSIs included in the study. The second approach of washing slides was applied to the development cohorts where we had control over the scanning process, namely STHLM3 and SUH. In the RUMC cohort, we excluded slides with pen marks on the tissue based on the findings of the participants in the PANDA challenge.

### Representative sampling

A key issue in the evaluation of diagnostic tests is how disease prevalence influences estimates of statistical measures used to assess the diagnostic performance of the tests. Prevalence is generally defined as the proportion of individuals in a population who have a particular disease at a given time. However, more specifically, the prevalence relates to the datasets used for evaluating a diagnostic test.

The positive predictive value (PPV; ie, the probability that individuals with a positive test result truly have the disease), negative predictive value (NPV; ie, the probability that individuals with a negative test result truly do not have the disease) and the Cohen’s kappa statistics are influenced by the disease prevalence in the datasets used for evaluating the performance of diagnostic tests. As prevalence increases, the PPV of a test also increases; and conversely, NPV decreases with increasing prevalence. This relationship means that in datasets where a disease (or disease subtype) is more common, the test’s ability to identify true positives increases and true negatives decreases. Similarly, the disease prevalence and case mix will impact estimates of Cohen’s kappa.

In contrast to PPV, NPV and Cohen’s kappa, sensitivity (also known as true positive rate, that is, the ability of a test to correctly identify patients with the disease) and specificity (also known as true negative rate, ie, the ability to correctly identify those without the disease) are not affected by changes in prevalence. These measures are intrinsic properties of the test and do not depend on how common the disease is in a population or dataset.

The sampling scheme or experimental design impacts the estimated prevalence in a study, thereby affecting the diagnostic performance statistics that are sensitive to prevalence. For example, in case–control studies, the prevalence is artificially set by the researcher. In datasets collected for the development of diagnostic AI systems (such as the one described in this protocol), it is common to upsample patients with a disease or disease subtype. If a consecutive case series were used for training an AI system to perform Gleason scoring, a very large set would be required in order to ensure a sufficiently large subsample of, for example, GS 9 and 10 samples for efficient training. Similarly, convenience sampling, where subjects are selected based on their availability rather than at random or according to a defined study design, can lead to a sample with a prevalence rate that does not match the general population. These types of experimental designs and sampling schemes can lead to assessments of PPV, NPV and Cohen’s kappa that do not reflect estimates that would be obtained in a consecutive case series in the general population.

The impact of prevalence on performance estimates underlines the importance of carefully considering the design of diagnostic studies. When prevalence is expected to differ, adjustments or different interpretations of PPV and NPV may be necessary to avoid misinformative conclusions. The data we use for training and evaluation of the AI system is a mixture of convenience samples (AMU, AQ, KUH-2, RUMC, SPROB20, STG) and data representing consecutive clinical cases or another well-defined and controlled sampling scheme (AUH, KUH-1, MLP, MUL, SCH, SFI, SFR, STHLM3, SUH, UKK, WNS). For the datasets with a known sampling scheme and experimental design, we can use prior probability shift corrections to achieve estimates of PPV, NPV and Cohen’s kappa on a well-defined base population.^52 53^

